## Standard of care framework

Irrespective of group allocation, all participants receive the institutional standard multimodal anesthesia and analgesia protocol, which is managed by the Acute Pain Service. Intraoperatively, all patients undergo a standardized general anesthesia regimen, including continuous hemodynamic monitoring (5-lead electrocardiogram, pulse oximetry, non-invasive and invasive arterial blood pressure) and controlled mechanical ventilation. Crucially, to provide preventive analgesia and mitigate the neuroendocrine stress response associated with major surgical trauma, early analgesic interventions—incorporating regional techniques such as thoracic epidural placement (T5-T12) or fascial plane blocks, tailored to the specific surgical approach—are systematically performed immediately following anesthetic induction and prior to the surgical incision. Postoperatively, this regimen employs a balanced strategy integrating peripheral analgesics, nonsteroidal anti-inflammatory drugs, and targeted opioid administration. In the immediate postoperative phase, pain is controlled through intravenous morphine titration, consisting of 2 mg boluses administered every 5 to 10 min until a Visual Analogue Scale score below 3 is achieved.

Subsequently, analgesic maintenance is provided via Patient-Controlled Analgesia pumps. These devices utilize a standardized 0.5 mg/ml morphine solution, programmed for demand boluses of 0.5 to 1.0 mg with a 7 to 15 min lockout interval. Furthermore, pain intensity is systematically evaluated as a vital sign during routine hemodynamic checks utilizing the Visual Analogue Scale (VAS). Concurrently, the Richmond Agitation-Sedation Scale (RASS) is monitored by the ICU clinical team as a safety and eligibility parameter. To ensure protocol fidelity and patient safety, a Virtual Reality session is only initiated if the patient is in an optimal state of alertness, defined as a RASS score between −1 (drowsy) and +1 (restless). Patients presenting with severe agitation (RASS ≥ +2) or deep sedation (RASS ≤ −2) will have their sessions postponed until clinical stabilization. Consequently, the uniform application of this baseline framework across all study arms ensures that any variations in cumulative opioid consumption can be attributed directly to the digital interventions being investigated.

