Researchers provide a training phase to ensure the patient is comfortable with the hardware and the virtual environment. Within this framework, the voluntary acceptance of the informed consent form serves as a natural filtration mechanism for technological affinity; by enrolling only participants who express interest and comfort with immersive digital activities, the study ensures a cohort predisposed to optimal therapeutic engagement, thereby mitigating potential variance related to prior gaming experience. Furthermore, to guarantee methodological consistency and eliminate behavioral bias, all research personnel undergo a standardized training program in accordance with Good Clinical Practice guidelines. The recruitment team, responsible for administering the informed consent form, is trained on the study rationale and experiences the virtual reality therapy to ensure standardized and neutral patient communication. Similarly, the bedside clinical team, tasked with conducting the sessions and collecting hemodynamic data, receives formal instruction emphasizing the critical importance of measurement accuracy. These professionals also complete hands-on simulation modules with the specific applications to assist patients with hardware operation. Finally, the data management team is trained on data extraction from both the institutional electronic health record system (Si3) and the bedside case report forms detailing the specific events of each therapeutic session. This rigorous training ensures the standardized transposition of all clinical variables into the REDCap platform, guaranteeing fidelity and traceability in data handling.

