In parallel, as a crucial secondary clinical outcome, pain intensity is measured using the Visual Analogue Scale (VAS) at rest and during movement, which is specifically elicited by instructing the patient to take a deep breath. Evaluating dynamic pain represents the clinical gold standard, as joint practice guidelines from the American Pain Society and the American Society of Anesthesiologists emphasize that assessing pain during movement or activity is essential to accurately capture postoperative discomfort and guide functional recovery [21]. These VAS assessments are conducted at predefined and standardized time points throughout the day, ensuring temporal consistency across all three study arms. To clarify the Prospective Randomized Open, Blinded Endpoint (PROBE) design, we have explicitly defined the blinding status of all involved personnel. Due to the physical and highly visible nature of the Virtual Reality headsets, complete double-blinding is structurally impossible. Therefore, to mitigate detection and performance bias, a strict blinding matrix is established (Table 1).

**Table 1 tbl0001:** Blinding matrix for the PROBE design.

Role	Blinding Status	Justification / Mitigation Strategy
Participants	Unblinded	Inherent to the use of highly visible VR equipment.
VR Application Team	Unblinded	Researchers responsible for device setup and safety monitoring.
ICU Clinical Team	Unblinded	Cannot be blinded due to the shared, open ICU environment.
Pain Outcome Assessors	Blinded	Distinct staff exclusively assessing VAS. Patients are instructed daily not to discuss VR.
Statistician	Blinded	Data delivered with masked group codes (e.g., Group A, B, C).

By completely separating the personnel who administer the VR sessions from the clinical professionals who assess the Visual Analogue Scale (VAS) scores, the outcome assessors remain blinded to the assigned intervention. Additionally, the primary endpoint (cumulative opioid consumption) is quantified objectively via automated PCA pump logs and standardized medical records, structurally preventing expectancy bias from the outcome assessors.

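### The described procedures do not secure blinded assessment of VAS pain, and a self-rating by unblinded patients cannot be reported as a blinded endpoint

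*Protocol article*

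**What the plan says.** Study design and randomization labels the trial PROBE. Clinical endpoints and blinding explains that label through a blinding matrix (Table 1). The row for pain outcome assessors reads "Distinct staff exclusively assessing VAS. Patients are instructed daily not to discuss VR", with status blinded. The text below the table gives the mechanism, "By completely separating the personnel who administer the VR sessions from the clinical professionals who assess the Visual Analogue Scale (VAS) scores", and the result, "the outcome assessors remain blinded to the assigned intervention". The same section has the outcome VAS taken at rest and on a deep breath, at fixed times common to the three arms.

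Table 1 also lists participants as unblinded. It lists the ICU clinical team as unblinded, with the reason "Cannot be blinded due to the shared, open ICU environment". The unblinded VR application team is described as "Researchers responsible for device setup and safety monitoring".

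Other sections describe related tasks:

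- Trial procedures and data collection refers to "the bedside clinical team, tasked with conducting the sessions and collecting hemodynamic data".
- Standard of care framework says that "pain intensity is systematically evaluated as a vital sign during routine hemodynamic checks". Virtual reality interventions repeats that pain is scored at each vital-sign check and uses the score to trigger rescue.
- Limitations concedes that the absence of blinding may bias how patients report VAS.

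**The concern.** A PROBE label tells the reader that treatment is open but that whoever determines the endpoint does not know the arm. For pain, the article supports that with a staffing rule. Two questions decide whether the rule delivers. Can the recorder stay unaware of the arm in this setting? And is the recorder the person who determines the score?

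The article calls VAS a crucial secondary outcome, and Background names pain intensity in the primary objective beside opioid consumption. If pain is published as a blinded endpoint when it is not one, readers will give a difference between arms more protection against expectancy and detection bias than the design provides. If it is also unclear which VAS readings are analysed, scores taken by unblinded staff could enter an analysis described as blinded.

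**Working it through.** The document gives no figure to reproduce, and no sample size, power or error rate is involved. The check sets the statements side by side.

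**1. Does the setting allow the recorder to stay blinded?** Table 1 gives the shared, open unit as the reason ICU staff cannot be blinded. While the patient is in the ICU, pain assessors work in the same space. The stated protections are distinct staff used only for VAS, their separation from session personnel, and a daily instruction to patients not to talk about VR. None of these stops an assessor from seeing a headset or a session in progress. Exposure is not brief: three sessions a day of 30 to 45 min give 3 × 30 = 90 min (1.5 h) to 3 × 45 = 135 min (2.25 h) per VR patient per day. Safety protocols and physical restrictions keeps a professional at the bedside throughout each session. With 1:1:1 allocation of 60 patients, 40 are in a headset arm. These figures show that sessions are visible; they do not estimate how often an assessor learns the arm.

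**2. Who determines the score?** VAS is the patient's own rating. Table 1 lists participants as unblinded. Whatever the recorder knows, the person producing the number knows the arm. Limitations accepts the consequence for VAS. This step needs no inference about staffing.

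**3. Are the roles consistent?** Table 1 gives device setup and safety monitoring to researchers. Trial procedures and data collection gives the conduct of sessions to the bedside clinical team. The two descriptions may overlap, but they do not match, so the group from which assessors must be kept separate is not clearly defined.

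**4. Is the outcome VAS distinguished from the routine VAS?** Two VAS measurements are described:

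| | Routine VAS | Outcome VAS |
|---|---|---|
| Where described | Standard of care framework; Virtual reality interventions | Clinical endpoints and blinding |
| When | At routine vital-sign checks | At predefined times in all arms |
| Who | Not named | Distinct assessors |
| Purpose | Care, including rescue | Secondary outcome |

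The article never says that these are separate measurements or that only the second is analysed. Data are drawn from the electronic health record and from bedside forms on the therapy sessions; neither source is identified as the assessors' record.

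**5. Does the text put session staff in charge of the outcome VAS?** No. That would require joining the bedside team's collection of hemodynamic data to the routine hemodynamic checks that include VAS. Clinical endpoints and blinding lists what is recorded around each session (heart rate, mean arterial pressure, oxygen saturation and respiratory rate), and VAS is not on that list.

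**The case against.** The strongest defence is that the article describes two compatible things: a clinical VAS that guides care, and a research VAS with its own conditions, times and dedicated assessors. On that reading nothing contradicts itself, and an explicit data-source rule is the sort of detail an article leaves to a fuller document. The defence adds that patient awareness is disclosed twice, in Table 1 and in Limitations, and that the article claims blinding for the assessors, not for the patient's rating.

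Much of this stands. The two-measurement reading is plausible, and staff separation is a real, stated safeguard. A reader might infer that the bedside team or session staff record the outcome VAS, perhaps around sessions; the document does not say so, and its list of session measurements omits VAS. A reader might also multiply sessions by patients to suggest a size of bias. Such a count assumes every session is completed and measures no bias.

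Two things survive. The article's own reason for unblinding ICU staff applies equally to assessors in the same unit, and staff separation does not answer it. And disclosing patient awareness does not reconcile it with a blinded-endpoint label: the matrix is offered as the clarification of PROBE, and for pain it blinds only the recorder of a self-report.

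**Conclusion.** The concern holds in this form: assessor blinding for VAS is claimed but not secured by the procedures described, and pain is a patient-reported outcome in an open trial, so it should not carry the blinded-endpoint label. The second part rests only on Table 1 and on VAS being a self-rating. The first assumes that assessors work in the open ICU during the period when sessions take place there; it does not show that unblinding will occur, or how often.

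The mismatch over who runs sessions, and the unstated relation between routine and outcome VAS, are ambiguities to be reconciled. They are not evidence that unblinded staff score the endpoint.

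The size of any expectancy or detection bias cannot be derived from the document. The point affects what may be claimed about a secondary outcome. A reader might extend it to the primary endpoint, cumulative morphine milligram equivalents from pump logs and medical records; nothing here addresses that endpoint.

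**What to change.** Reconcile Standard of care framework, Virtual reality interventions, Trial procedures and data collection, and Clinical endpoints and blinding, as follows:

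1. State who conducts the sessions, using the same role name in the procedures text and in Table 1.
2. State that the analysed VAS consists only of scores taken by the designated assessors at the predefined time points. They should not be taken by anyone running that patient's sessions, nor while the headset is on or being set up.
3. State that the routine vital-sign VAS serves care only and does not enter the endpoint.
4. Replace "the outcome assessors remain blinded to the assigned intervention" with wording such as: *patient-reported, open-label; recorder intended to be blinded*. Do not report VAS as a blinded endpoint.

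Optionally, have assessors record a guess of the arm at the last assessment and report it by arm. This is useful information but corrects no error.

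The cost is protocol wording and a data-source rule. No staff are added, since Table 1 already provides for distinct assessors, and the routine use of VAS in care is unchanged. The downside is that the stated blinding becomes less favourable.

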## Background

The management of postoperative pain in cardiothoracic surgery remains a critical challenge, as inadequate analgesia more than doubles the risk of postoperative complications (OR 2.56), including respiratory dysfunction and prolonged hospitalization [1]. Furthermore, while opioids represent the analgesic cornerstone, their dose-dependent administration induces adverse events in approximately 20% of patients, precipitating significant morbidity such as respiratory depression, emesis, and long-term dependence [2].

This proposed protocol addresses the clinical need for innovative, non-pharmacological adjuncts to multimodal analgesia. Grounded in the limited capacity theory of attention, highly immersive distractors exhaust finite cognitive resources, modulating shared cortical networks [3] and triggering neurochemical responses, such as endorphin release, to effectively reduce perceived pain intensity [4].

Virtual Reality (VR) provides a superior level of immersion compared to traditional distraction methods, yielding up to an 88% decrease in postoperative pain [5]. Therefore, this study is designed as a proof-of-concept efficacy trial to standardize VR application in the Intensive Care Unit (ICU) setting, targeting patients (16–40 years old) undergoing cardiothoracic surgery. Our primary objective is to evaluate the preliminary clinical efficacy of this multi-session VR protocol on cumulative opioid consumption and pain intensity. It distinguishes itself by evaluating two digital strategies—active gaming, associated with the attenuation of cortical pain-related amplitudes [6], and passive 360° video contemplation—to determine their respective impact on postoperative recovery.

By establishing this early-stage framework, this protocol provides researchers and clinicians with a reproducible model for integrating digital health technology into the perioperative period, emphasizing technical feasibility, equipment hygiene, and patient safety, while gathering preliminary efficacy signals to guide future definitive trials.

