## Sample size and study population

The fundamental rationale relies on the limited capacity theory of attention, positing that highly immersive multisensory environments exhaust finite cognitive resources to mitigate acute pain perception [7]. Furthermore, as demonstrated by Lier et al., virtual reality yields significant overall analgesic efficacy (SMD = −0.65), with particularly robust effects observed among younger demographics [8]. Consequently, the trial enrollment focuses on 60 patients aged 16 to 40 years. Eligible procedures include cardiac and specific thoracic surgeries, such as pulmonary decortication, video-assisted thoracoscopic surgery (VATS), lung biopsy, and Nuss bar pectus excavatum repair.

As this trial is designed as an early-stage, proof-of-concept efficacy study in the specific context of cardiac surgery, a formal a priori power calculation for clinical efficacy is not performed. Instead, a pragmatic sample size of 20 patients per arm (total N = 60) is established. This sample size is aligned with phase IIa / proof-of-concept trials aimed at detecting large clinical effect sizes, evaluating the safety profile of the intervention, and providing initial estimates of variance (mean and standard deviation) to adequately power future, large-scale definitive multicenter trials.

While previous studies have demonstrated substantial effect sizes for VR analgesia in other surgical contexts, extrapolating those parameters to a three-arm, highly invasive cardiothoracic population is not methodologically sound for an a priori power calculation. Therefore, this sample size of 60 serves as a pragmatic and methodologically sound approach. It is sufficiently large to evaluate our primary feasibility metrics and safety profiles, while providing exploratory signals regarding the cumulative opioid consumption to inform future research.

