## Virtual reality interventions

For the intervention arms, a progressive additive model is applied to ensure clear methodological differentiation. Group 3 serves as the control and receives the institutional standard multimodal anesthesia and analgesia protocol. To maintain high external validity and reflect real-world intensive care conditions, pharmacological management and rescue analgesia for all groups are strictly governed by the institutional Standard Operating Procedure for Acute Pain Management. According to this protocol, pain is objectively assessed during every routine vital sign check. Adequate pain control is institutionally defined as a Visual Analogue Scale (VAS) score of 3 or less. Consequently, subjective bedside dosing is minimized, as any reported pain score of VAS ≥ 4 (categorized as moderate to severe pain) triggers mandatory re-evaluation and the administration of standardized rescue interventions—including oral, intermittent intravenous, or PCA titrations—until the target of VAS < 3 is achieved. Furthermore, to preserve the pragmatic nature of the trial, participants in the control group are not restricted from using standard non-immersive personal devices, such as smartphones or hospital televisions. Restricting access to these devices is considered ethically and logistically inviable due to the essential need for family communication during a critical postoperative period and the inherent setup of shared hospital rooms. Therefore, this study is pragmatically designed to evaluate the supplementary efficacy of virtual reality immersion against the baseline noise and unstructured digital distractions that already constitute the real-world standard of care. This methodological allowance is further grounded in the premise that the therapeutic mechanism of virtual reality relies on multisensory immersion, which fundamentally differs from the limited cognitive engagement provided by conventional two-dimensional screens.

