Alongside these daily clinical assessments, the safety and tolerability of the intervention are continuously evaluated. Hemodynamic and respiratory parameters, comprising heart rate, mean arterial pressure, oxygen saturation, and respiratory rate, are recorded immediately before and after each virtual reality session. The research team actively monitors for signs of cybersickness, such as nausea or dizziness, as well as physical adverse events ranging from neck pain to skin lesions caused by the headset. Consequently, safety and hygiene protocols, which have been approved by the Hospital Infection Control Committee (CCIH), are paramount for trial replication. The equipment undergoes a cleaning process involving the disinfection of the headset's external hard plastic surfaces with 70 percent isopropyl alcohol wipes. To preserve structural integrity and prevent degradation of the anti-reflective coatings, the VR optical lenses and the auxiliary mirroring tablet screens are cleaned using a specific non-alcoholic optical screen cleaning solution (Implastec, Brazil) applied with dry microfiber cloths. To prevent cross-contamination, patients are provided with specific disposable ocular masks designed for virtual reality headsets. Furthermore, the head straps are wrapped in a protective plastic film that is replaced between each patient use. Throughout the process, the protocol allows for immediate cessation of the session if any discomfort arises. Moreover, in the unlikely event of a serious or unanticipated adverse reaction, the research team is mandated to halt the intervention immediately, provide appropriate medical care, and report the incident to the Institutional Review Board within 24 h, in compliance with ethical guidelines.

Furthermore, broader secondary clinical trajectories and major postoperative complications are monitored to provide a comprehensive recovery profile. The study tracks the length of stay in both the intensive care unit (ICU) and the hospital, the total cumulative duration of mechanical or noninvasive ventilation required throughout the ICU stay, and the incidence of critical events such as delirium, assessed via the CAM ICU protocol, or paralytic ileus.

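### Safety recording is built around VR sessions, and no matching nausea, dizziness or vital-sign collection is described for the control arm

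*Protocol article*

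**What the plan says.** The safety paragraph of the protocol article, under Clinical endpoints and blinding, opens by saying that "the safety and tolerability of the intervention are continuously evaluated". Heart rate, mean arterial pressure, oxygen saturation and respiratory rate "are recorded immediately before and after each virtual reality session". On symptoms it says "The research team actively monitors for signs of cybersickness, such as nausea or dizziness", and it adds neck pain and headset skin lesions. In Table 1 the unblinded VR Application Team is described as "Researchers responsible for device setup and safety monitoring".

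For the control arm, Virtual reality interventions says "Group 3 serves as the control and receives the institutional standard multimodal anesthesia and analgesia protocol". Group 3 therefore has no sessions to which these recordings could attach.

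Opioid exposure is common to all arms. Standard of care framework says "Irrespective of group allocation, all participants receive the institutional standard multimodal anesthesia and analgesia protocol", which includes intravenous morphine titration followed by patient-controlled analgesia. On opioids, Background says "their dose-dependent administration induces adverse events in approximately 20% of patients", and it names emesis among the harms. Sample size and study population lists "evaluating the safety profile of the intervention" among the aims that the 60 patients are meant to serve.

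**The concern.** Nausea and dizziness are not specific to VR. Patients on morphine after cardiothoracic surgery have them too, and the article's own opioid figure implies that some will occur in every arm. The article names these symptoms in advance as signs of cybersickness, gives safety monitoring to the team running the headsets, and ties the study's vital-sign recordings to sessions. A symptom rate collected on that basis has no concurrent control rate beside it.

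Two questions then go unanswered. Does VR add nausea or dizziness? Or does it remove some by reducing opioid use, which is the rationale of the trial? An analysis plan written later cannot repair this, because control data that were never collected cannot be recovered.

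**Working it through.** **The article's own safety figure.** Protocol validation reports one mild dizziness event in the pilot: 1/45 sessions = 2.2% and 1/3 patients = 33.3%. Both reproduce, as does 3 patients × 15 sessions = 45. The exact 95% intervals are 0.06% to 11.8% per session (treating sessions as independent) and 0.8% to 90.6% per patient. The pilot had VR patients only, so it gives no background rate.

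**What is described for each arm.**
- *Study vital signs.* They are anchored before and after each session, so the schedule cannot apply to Group 3.
- *Nausea and dizziness.* The research team monitors them as cybersickness. No schedule or arm is named.
- *Study forms.* Trial procedures and data collection names two sources: the electronic record, and bedside forms on the events of each therapeutic session. No bedside form for patients without sessions is described.
- *Contrast with pain.* VAS is taken at standardized times in all three arms. The safety paragraph has no such statement.

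**Size of the background (assumption).** The 20% covers all opioid adverse events, so using it for nausea and dizziness is an assumption. I show 10% to 30%. There are 20 patients per arm, hence 40 VR and 20 control. Assume no VR effect and that every case over the course is captured. Expected VR cases = 40 × p:

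| p | VR cases expected (95% binomial range) | Control cases expected |
|---|---|---|
| 10% | 4 (1 to 8) | 2 |
| 20% | 8 (3 to 13) | 4 |
| 30% | 12 (7 to 18) | 6 |

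Without a control rate, 8/40 would stand alone as 20% (exact 95% CI 9.1% to 35.6%), although VR contributed nothing.

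**What equal collection would give.** Half-width = 1.96 × √[p(1−p)(1/40 + 1/20)]. At p = 0.2 this is 1.96 × √(0.16 × 0.075) = 1.96 × 0.1095 = 0.215, or about 21 points. With 8/40 against 4/20, the Newcombe 95% interval for the difference of 0 is about −24 to +19 points. Power with 40 VR and 20 control patients is about 33% for 20% versus 40%, and about 87% for 20% versus 60%.

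**The case against.** A reader might infer more than the article supports, and several objections stand.

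- *Symptoms are collected only at sessions.* The before-and-after wording governs vital signs alone. The symptom sentence names no session, schedule or arm, and the paragraph speaks of continuous evaluation. Session-only collection of symptoms is an inference, though a reasonable one from the session-based forms and Table 1.
- *Opioid symptoms will be counted as VR harm.* No attribution rule is stated either way. A professional attends every session, so onset relative to VR can be observed, and vital signs have a within-patient contrast.
- *Group 3 has no safety data.* This is too strong. Routine vital-sign checks occur in all arms, records are extracted, and delirium and paralytic ileus are tracked without a link to sessions.
- *A count of 40 × 15 = 600 symptom checks against none.* The article does not specify one symptom check per session. Likewise, the case counts in the table assume capture over the whole course, whereas VR time is at most 11.25 h, about 9% of five days (11.25/120).
- *The missing-data sensitivity analysis rests on the cybersickness label.* The article cites cybersickness only as an example of why dropout may be asymmetric. Pattern-mixture models work on dropout patterns and do not need symptoms to be attributed.

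It can also be said that a condensed article leaves adverse-event forms to the full protocol, and that the comparison would be imprecise. The first point does not dispose of the matter, because the article does state a collection rule and anchors it to sessions. The second is true, and limits the gain to description.

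**Conclusion.** The point holds in a limited form. The safety recording that the article describes is organised around VR sessions and the VR team, and no matching collection of nausea, dizziness or study vital signs is described for Group 3. Since all arms receive opioids and safety is a stated aim, the trial as described cannot separate VR-related nausea or dizziness from opioid or postoperative symptoms, or show a benefit through opioid sparing.

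The illustrative size is 4 to 12 of 40 VR patients with such symptoms and no VR effect. It rests on an assumed background rate of 10% to 30% and on full capture. Equal collection would not settle the question: at 20% per arm, the 95% half-width of about 21 points cannot exclude a doubling of the rate. It would give a descriptive comparison for planning a larger trial. The primary endpoint and its analysis are not affected.

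**What to change.** In the safety paragraph of Clinical endpoints and blinding:

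1. Record nausea and dizziness, in the same neutral wording, at the routine vital-sign checks that already take place in all three arms. The ICU clinical team should do this. The blinded pain assessors should not, because Table 1 restricts them to VAS scoring and questions about headset-type harms could unblind them.
2. For Group 3, extract routine vital signs at times matched to the VR sessions.
3. Report nausea and dizziness by arm, with confidence intervals for VR minus control, as descriptive results.
4. Keep session-linked cybersickness, neck pain and headset skin lesions as VR-only descriptive counts collected by the VR team.

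The cost is a short added item at checks already made, the matched extraction, and one table. The ICU team is unblinded, so ascertainment of these symptoms would be unblinded too, and the limitations should say so. The change needs to be in place before enrolment.
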